#### Pilot Evaluation: Changes Made From Pilot to RCT

In a pilot study in 2012, we tested an intervention based on MI and medication review aimed at improving patients’ beliefs about medicines and adherence to secondary prevention of cardiovascular disease [41]. The pilot RCT of 21 patients resulted in insights regarding the feasibility of the intervention and study design. Patients with more negative beliefs (BMQ-S) changed toward more positive beliefs, but there was no difference between groups at follow-up. A need to stratify the randomization based on baseline beliefs was identified [41]. We tested a method of categorizing patients according to their beliefs in the pilot study population and found that half of the population (10 patients) had an attitude with a potentially negative impact on adherence [42].

In line with the recommendation from the Medical Research Council (MRC) [3], we have also made a qualitative evaluation of the pilot study (not published). Interviews of 8 patients showed that, overall, the patients were positive about the intervention and felt more informed by it. The interviews also informed us that some patients changed their views on medicines in a positive direction, although it was not enough to categorize them to an attitude group with higher adherence. The care processes for these 8 patients were also compared with the theoretical framework of the intervention, and we found that all the patients were affected by some part of the intervention; patients with a negative attitude toward their medicines were mainly affected in the adherence dimensions, whereas patients with a positive attitude were helped in the area of quality of treatment. However, our evaluation showed that not all the dimensions of adherence were well covered in the identification phase of the intervention and that the pharmacist felt the need for more training in MI.

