#### Study Design of the RCT in Brief

The MIMeRiC trial is an RCT with 2 parallel groups (N=418) and 12 months follow-up. Patients with CHD identified and followed at the cardiology clinic of Kalmar County Hospital are randomized to usual care (control) or usual care plus a follow-up program with medication review and MI. Ethical approval has been obtained from the Regional Ethics Committee, Linköping (Dnr-2013/236-31). The trial (clinicaltrials.gov, NCT02102503) has been fully described in the forthcoming protocol [6]. Patients in the intervention group meet a clinical pharmacist at the cardiology clinic 2 to 5 times during the year after discharge depending on need, and problems with adherence or prescribing are solved in collaboration with the patient and/or the cardiologist.

The primary outcome of the trial is the proportion of patients reaching the treatment goal for low-density lipoprotein cholesterol. Secondary outcomes involve the effects on blood pressure, patient adherence, quality of life, and health care use. An economic evaluation of the intervention is also planned.

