### Methods for Research Question 5: Did the Intervention Change the Patients’ Beliefs About Their Cardiovascular Medicines?

This will be studied primarily quantitatively, but certain aspects will also be illustrated qualitatively by the interviews with patients.

Data on beliefs about medicines will be collected in the MIMeRiC trial with the BMQ-S instrument administered 3 times: baseline (after the standard care follow-up), after 10 months (during the intervention), and after 15 months (after the intervention). In this study, we will ask the patients to consider only their heart medicines as they answer the BMQ-S. The instrument consists of two subscales, one for the perceived necessity for the drugs and one for perceived concerns about the drugs. The two subscales have 5 items each and are assessed by a 5-point verbal descriptor scale ranging from strongly disagree to strongly agree.

As instructed by the originators, numerals (1-5) will then be assigned to each statement of agreement to summarize each subscale with 5 to 25 points. The difference between the necessity and concern scales (range: −20 to 20) will then be related to the cost-benefit analysis for each patient’s medications. A positive difference means that the patient perceives the benefit of taking the drugs to outweigh the risks of taking the drugs, and the more positive the difference is, the more adherent the patient is supposed to be [9]. It has also been found that categorization based on high (>15) or low (<15) scores on each scale, yielding 4 categories (accepting, ambivalent, neutral, and skeptical) predicts adherence behavior [46,47]. Because the scales have ordered verbal categories, it is not correct to assign numerals and sum them to a global score, because the data are only ordered within the structure while the distance between the agreement statements or the magnitude of them is not known [48]. Even though the categorization also depends on the global sum of each scale, this is a more correct way of handling the data. Therefore, we chose this as our primary outcome in analyzing the effects of the intervention on beliefs. The stratified randomization of patients in the MIMeRiC trial was also based on these four categories.

In this study, we will:

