analyze whether there is a difference between the control group and the intervention group in the proportion of patients in each category at follow-up (15 months)describe temporal changes in the 4 categories over the 3 assessments in the control and the intervention groupsanalyze changes in the sum of each subscale, and differences between the intervention and control groupsanalyze changes in each item of the scales, and differences between the intervention and control groupsanalyze the transcribed material from the focus group interviews with intervention patients described above using deductive content analysis methods, based on the 10 items of BMQ-S, as a way of including the results of the quantitative study of beliefs

While item 1 in the list is a primary objective, items 2 to 5 refer to secondary objectives.

Analyses 1 to 3 will be adjusted for variables thought to be influential: sex, age, type of CHD, and history of CHD. In our pilot study, most patients with an ambivalent attitude toward their drugs had a history of CHD [42].

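### The primary beliefs analysis (research question 5, analysis 1) is not adjusted for baseline BMQ-S category, the randomisation stratum and the outcome's own baseline value; the error is conservative and costs power

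*Protocol article*

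**What the plan says.** All of this is in the protocol article. Under Methods for Research Question 5, the four BMQ-S categories (accepting, ambivalent, neutral, skeptical) are the main outcome for beliefs: "Therefore, we chose this as our primary outcome in analyzing the effects of the intervention on beliefs". The next sentence says: "The stratified randomization of patients in the MIMeRiC trial was also based on these four categories". The section on the pilot gives the reason: "A need to stratify the randomization based on baseline beliefs was identified".

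BMQ-S is measured three times: "baseline (after the standard care follow-up), after 10 months (during the intervention), and after 15 months (after the intervention". The first listed analysis, named as the primary objective, looks for a "difference between the control group and the intervention group in the proportion of patients in each category at follow-up (15 months". Analysis 2 describes category changes over the three assessments, analysis 3 concerns changes in the subscale sums, and analysis 4 concerns changes in single items.

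The adjustment sentence reads: "Analyses 1 to 3 will be adjusted for variables thought to be influential: sex, age, type of CHD, and history of CHD". Neither the baseline category nor a baseline score is named.

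**The concern.** The design and the analysis treat baseline beliefs differently. Baseline beliefs mattered enough to stratify on, yet they are missing from the list of influential variables. The omitted variable is also the baseline measurement of the outcome, and it must have been known for each patient before stratified allocation.

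Stratifying removes chance imbalance in baseline category, so the treatment difference varies less from trial to trial. A model without the stratum does not know this and reports a standard error as if allocation had been unstratified. Confidence intervals are then too wide and the test rejects too seldom. Research question 5 is meant to help explain why the intervention did or did not work, so a missed effect on beliefs would mislead that explanation.

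**Working it through.** **Figures in the article.** There is no power calculation, effect size or correlation for research question 5, so there is no stated figure to reproduce. The size of the trial comes from the brief design section: "The MIMeRiC trial is an RCT with 2 parallel groups (N=418) and 12 months follow-up".

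**Assumptions.** 1:1 allocation (418 / 2 = 209 per group), two-sided 5%, no dropout. For power, 50% versus 60% in the accepting category. The 50% echoes the pilot, which "found that half of the population (10 patients) had an attitude with a potentially negative impact on adherence"; the 10-point difference is only an illustration.

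**Step 1: how much the baseline category explains.** Correlated baseline and follow-up subscale scores were simulated with 209 per group (assumed necessity mean 20, SD 3.5; concerns mean 13.5, SD 4). The ratio V of adjusted to unadjusted variance for the accepting-versus-other difference was 0.91, 0.86 and 0.79 at score correlations of 0.5, 0.6 and 0.7. The share explained is R² = 1 − V, or 9%, 14% and 21%.

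**Step 2: consequences for analysis 1.** With allocation balanced on the stratum, the true variance is V times the variance that the unadjusted model reports.
- Overstatement of the standard error: 1/√V.
- True size of a nominal 5% test: 2 × (1 − Φ(1.96/√V)).
- Unadjusted standard error at 50% versus 60%: √((0.25 + 0.24)/209) = 0.0484, so the standardised difference is 0.10/0.0484 = 2.065.
- Power without the stratum: Φ((2.065 − 1.96)/√V). With it: Φ(2.065/√V − 1.96).

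| Score correlation | V | SE too large by a factor of | True size | Power without stratum | Power with stratum | Equivalent N = 418/V |
|---|---|---|---|---|---|---|
| 0.5 | 0.91 | 1.05 | 4.0% | 54% | 58% | 459 |
| 0.6 | 0.86 | 1.08 | 3.5% | 55% | 61% | 486 |
| 0.7 | 0.79 | 1.13 | 2.7% | 55% | 64% | 529 |

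**Step 3: check by simulation.** A separate simulation used four strata, assumed permuted blocks of 4, N = 418 and 1,500 runs per scenario.
- R² = 0.256, no effect: the empirical SD of the estimate was 0.0415 with or without the stratum, but the mean reported standard error was 0.0489 without it and 0.0422 with it. Rejection rates were 1.9% and 4.0%. For a 10-point effect, power was 58% and 69%.
- R² = 0.087: differences were small. Rejection rates were 4.7% and 5.8%, and power 55% and 58%. Monte Carlo error on a 5% rate is about √(0.05 × 0.95/1500) = 0.6 points.

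The mechanism is confirmed: the estimate already benefits from stratification, and it is the reported uncertainty that is wrong. R² = 0.256 lies a little above the range in step 1.

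**Step 4: analysis 3.** A change score already subtracts baseline. In units of the single-visit variance, its variance is 2(1 − r), against 1 − r² when the follow-up score is adjusted for baseline. The ratio is (1 + r)/2, so the further reduction is (1 − r)/2: 25% at r = 0.5, 20% at 0.6 and 15% at 0.7. The corresponding factors for the standard error, √(2/(1 + r)), are 1.15, 1.12 and 1.08.

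**The case against.** The strongest defence is that stratified allocation already balances baseline category at entry, the remaining error is conservative, and research question 5 is a process question rather than the trial's primary outcome, which is LDL cholesterol. This stands, and it limits the point to precision and calibration. It does not make the unadjusted standard error right.

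A second defence is that this is a condensed article and the separate RCT protocol may say how strata are handled. That is possible. But the article names its covariates for analyses 1 to 3 and presents itself as the prespecification of this evaluation, so a reader following it would omit the stratum.

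Third, the named covariates may recover part of the loss. The article reports that most ambivalent pilot patients had a history of CHD. The calculations above make no allowance for this.

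Several stronger readings are tempting but unsupported:
- A reader might infer that all the beliefs analyses ignore baseline. Analysis 2 is descriptive and includes the baseline assessment, analyses 3 and 4 concern change, and the adjustment sentence does not cover analysis 4.
- A reader might infer that analysis 3 forgoes r², or 25% to 49%, of the variance. That comparison is with a follow-up score alone; against the planned change score the gain is 25% falling to 15%.
- A reader might call baseline category the strongest predictor available. This is plausible for an outcome's own baseline value, but the article gives no correlation.
- A reader might infer bias from baseline imbalance among those who return the 15-month questionnaire. That would need differential non-completion, of which the article gives no evidence.

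**Conclusion.** The point holds for analysis 1, the primary objective of research question 5, and in weaker form for analysis 3. The omission is explicit and sits badly with the article's own stratified design. It makes inference conservative and does not inflate false positives.

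The size rests on the assumed score correlation of 0.5 to 0.7, the assumed score distributions, equal allocation and complete follow-up; a weaker correlation would make the loss in analysis 1 smaller. Within that range the loss is modest. It is still worth removing, because the baseline data are collected anyway and some outcome results may be known before this analysis is done, when a covariate added late would look post hoc.

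**What to change.** Rewrite the adjustment sentence under Methods for Research Question 5:
- Analysis 1: add baseline BMQ-S category (the randomisation stratum) to sex, age, type of CHD and history of CHD.
- Analysis 3: add the baseline value of the subscale concerned, and the stratum.

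The cost is one sentence and no new data. There are two small downsides to settle in the same text. Four baseline categories against a four-category outcome may leave sparse cells, so state in advance how categories will be combined. If a logistic model is used, the adjusted odds ratio is conditional on the covariates, so report the effect as an adjusted risk difference to keep the comparison one of proportions.

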### Methods for Research Question 6: How Did the Intervention Affect the Patients’ Experience of Their Follow-Up Care After CHD?

This is a qualitative study of how patients perceive their care after discharge from hospital following CHD. An open question will be enclosed with the questionnaires sent at the 15-month follow-up to all patients enrolled after January 1, 2016. The instructions to these patients will be: *Please take a moment to write freely about your view of the follow-up care you received after your myocardial infarction or angina*

### Methods for Research Question 7: Did the Intervention Change the Quality of Prescribing?

This will be studied using quantitative methods. There are several models for assessing the appropriateness of prescribing or medication use which have been used in intervention studies of medication reviews [49,50]. For this study with a selected group of patients with CHD, we chose to use a tool developed for this diagnosis: the Medication Assessment Tool for evaluation of secondary prevention of CHD (MAT-CHDsp) [51]. The tool is a summary of review criteria based on clinical guidelines and has been developed for use in clinical audits. Compared with the variables in the Swedish Quality Register SWEDEHEART, in which the proportion of patients with a prescription from a certain drug class is registered, MAT-CHDsp has a more individual application where prescriptions that do not follow the guidelines can be justified if the reason is stated in the EHR. The tool was updated in 2014 based on the European guidelines from 2011 and 2012 for myocardial infarction or acute coronary syndrome and the Swedish guidelines for heart disease from 2011 and was then validated in 22 patients in this study. MAT-CHDsp comprises 28 review criteria for which the assessor chooses *not applicable*, *yes*, *no*, *no information found*, or *no, but this is justified*. As an example, the treatment of a patient with CHD and no left ventricular (LV) dysfunction but with side effects from several statins documented in the EHR would be marked as *not applicable* for the criterion “Patient with CHD with LV dysfunction...is prescribed a beta-blocker” and *no, but justified* for the criterion “Patient with CHD is prescribed atorvastatin or simvastatin.”

The MAT-CHDsp will be applied to a random sample of 20% of the patients in each of the intervention and control group. Data on the prescribing 6 months after discharge will be collected retrospectively from the EHR at assessment. Applicable criteria will then be analyzed for adherence to guidelines or justified nonadherence. The results will be compared between the groups in terms of adherence and justified nonadherence, as a measure of the quality of the prescribing for secondary prevention [52].

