#### Management and Governance

The process evaluation is to be conducted in parallel with the MIMeRiC trial; some data will be collected together for the two studies. Data analysis for the two studies will also be conducted in parallel. The same researchers are responsible for the RCT, delivering the intervention, and planning and conducting the process evaluation; our small research team and restrictive funding did not allow for any independent evaluators to be involved [3].

Most of the research questions are covered by the ethical approval obtained for the RCT, but a supplemental ethical approval was granted for qualitative study of the patients’ experience of the intervention (interviews) and their views on the follow-up care after discharge (questionnaire).

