### Methods for Research Question 1: What Was Actually Delivered in the Medication Review?

This will be studied using a descriptive, quantitative method. The number and type of DRPs will be described using the 7 categories suggested by Cipolle and colleagues: (1) adverse drug reaction, (2) ineffective drug, (3) need for additional drug therapy, (4) dosage too low, (5) dosage too high, (6) unnecessary drug therapy, and (7) noncompliance. If acting on the DRPs has any effects that are documented in the electronic health record (EHR), these will also be described. Data are collected from the pharmacists’ documentation in the EHR and from separate study notes about DRPs that pharmacists record during the intervention. Data on the effects of actions on DRPs will be collected from the EHR; the pharmacists’ documentation will be used with laboratory results, documentation by primary care or other professionals at the cardiology clinic when relevant.

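### Research Question 7 credits a guideline deviation when a reason is in the health record, so justified nonadherence, and any sum including it, can differ between arms with identical prescribing

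*Protocol article*

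**What the plan says.** All references are to the protocol article.

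- **Scoring (Methods for Research Question 7).** "MAT-CHDsp comprises 28 review criteria for which the assessor chooses" one of five answers: *not applicable*, *yes*, *no*, *no information found*, or *no, but this is justified*. The section explains that "prescriptions that do not follow the guidelines can be justified if the reason is stated in the EHR". In its own example, a patient "with side effects from several statins documented in the EHR would be marked as" justified on the statin criterion.
- **Comparison (same section).** A random 20% of each group is assessed. Prescribing at 6 months after discharge is read back from the EHR, and the results are "compared between the groups in terms of adherence and justified nonadherence, as a measure of the quality of the prescribing".
- **Who writes in the record (Methods for Research Question 1).** Data on drug-related problems (DRPs) come from the pharmacists' "documentation in the EHR and from separate study notes about DRPs that pharmacists record during the intervention". Adverse drug reaction is the first of the seven problem categories.
- **Who meets a pharmacist (Study Design of the RCT in Brief).** Patients "are randomized to usual care (control) or usual care plus a follow-up program with medication review and MI". "Patients in the intervention group meet a clinical pharmacist at the cardiology clinic 2 to 5 times during the year after discharge".
- **Usual care (Pilot Evaluation: Changes Made From Pilot to RCT).** Patients normally have a cardiology visit about 2 months after discharge, at which effects and side effects of the medicines are evaluated.

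**The concern.** Whether a deviation counts as justified depends on what was prescribed and also on whether someone wrote down why. The intervention adds a professional whose work includes finding side effects and other drug problems and documenting them in the record from which the score is read. Randomisation does not balance this, because the extra documentation is a consequence of allocation. Two patients on the same drugs, with the same history of intolerance, can score differently because one had a pharmacist's note.

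Research Question 7 asks whether prescribing quality changed, and it is the article's between-group test of the route from medication review to prescribing. Under Integrating Results of Analysis, its answer will be combined with the others and applied to the trial results. A difference due to documentation could then be read as evidence that the review changed treatment, and be used to explain a cholesterol result that it did not cause.

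**Working it through.** The article gives no sample size, expected value or effect for Research Question 7, so there is no figure to reproduce. The check has two parts.

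**1. Can pharmacist notes reach the score?**

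- The rule accepts a reason stated in the EHR. Methods for Research Question 7 restricts neither the author nor the date of the entry.
- The standard visit is at about 2 months. The questionnaire in Methods for Research Question 2 places the pharmacist consultation after the physician follow-up. A pharmacist note can therefore be in the record before the 6-month point.
- A further consultation takes place at 10 months. Because the record is read retrospectively and no date limit is stated, a reason first written then could also be credited to 6-month prescribing.
- The control group receives usual care, and no pharmacist contact is described for it.

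The path from allocation to score is therefore open without any change in prescribing.

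**2. How large could the effect be?** Hold prescribing identical in both arms and let only documentation differ. Define:

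- a = share of applicable criteria scored *yes*
- j = share of deviations for which a valid reason exists
- d = probability that this reason is in the EHR (d_C for control, d_I for intervention)

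Then justified share = (1 − a) × j × d, sum = a + (1 − a) × j × d, and spurious difference = (1 − a) × j × (d_I − d_C).

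All values of a, j and d are assumptions; none comes from the article.

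| a | j | d_C | d_I | *Yes*, both arms | Justified, C vs I | Sum, C vs I | Difference (points) |
|---|---|---|---|---|---|---|---|
| 0.7 | 0.5 | 0.5 | 0.5 | 70% | 7.5% vs 7.5% | 77.5% vs 77.5% | 0 |
| 0.8 | 0.3 | 0.5 | 0.7 | 80% | 3.0% vs 4.2% | 83.0% vs 84.2% | 1.2 |
| 0.8 | 0.5 | 0.5 | 0.9 | 80% | 5.0% vs 9.0% | 85.0% vs 89.0% | 4.0 |
| 0.7 | 0.5 | 0.5 | 0.9 | 70% | 7.5% vs 13.5% | 77.5% vs 83.5% | 6.0 |
| 0.6 | 0.7 | 0.3 | 0.9 | 60% | 8.4% vs 25.2% | 68.4% vs 85.2% | 16.8 |

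For the fourth row: 0.3 × 0.5 × (0.9 − 0.5) = 0.06. The second and last rows are the extremes of the grid examined (a from 0.6 to 0.8; j from 0.3 to 0.7; documentation 0.5 vs 0.7, 0.5 vs 0.9 and 0.3 vs 0.9). With equal documentation the difference is zero throughout. The *yes* column never moves.

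**Could such a difference look significant?** The sample is 0.20 × 418 = 83.6 patients, about 42 per arm if allocation is 1:1 (the ratio is not stated). For the 6-point case, treating criteria as independent and testing the sum at two-sided 5%, the chance of a significant result is about 34%, 59% and 77% with 5, 10 and 15 applicable criteria per patient (210, 420 and 630 criteria per arm). Criteria within a patient are correlated, so these chances are probably too high. For example, a design effect of 2 with 10 criteria leaves 420 / 2 = 210 effective criteria per arm, which takes 59% back to about 34%.

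**The case against.** **Justified deviation belongs to the construct.** The legend to Multimedia Appendix 1 makes individualisation, alongside guideline adherence, a determinant of prescribing. Theoretical Framework for Intervention Design warns against improving adherence to a treatment that may do harm. A review that uncovers a side effect and leads to a reasoned deviation is working as intended, and counting only *yes* would score that as failure. This stands. It rules out replacing the comparison with *yes* alone, so both components have to be shown.

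**The comparison may already be two results.** The wording does not say whether adherence and justified nonadherence are summed or reported side by side. If side by side, *yes* is not inflated by this rule. This also stands, and it limits the point to the justified component and any sum. The justified component is still offered as a measure of prescribing quality, so the problem does not disappear.

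**The asymmetry is one of degree.** A reader might infer that pharmacists write only in intervention records and that controls have no comparable entry. The article does not say so. The contrast is inferred from the usual-care description, and the routine visit at about 2 months gives both arms an opportunity to record intolerance. The article also says that pharmacists document drug-related problems, partly in study notes kept apart from the EHR. It does not say that they record reasons for deviating from guidelines.

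**The direction is not guaranteed.** Fuller notes can turn *no information found* or *not applicable* into a plain *no*, for instance by recording an untreated condition, which would lower the intervention score.

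**The assessors.** Management and Governance states that "The same researchers are responsible for the RCT, delivering the intervention, and planning and conducting the process evaluation", and a reader might infer that those who wrote the notes will also score them. The article does not say who applies MAT-CHDsp in this comparison, and the coding of motivational interviewing was sent to an outside institute. The point does not depend on who scores.

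**Conclusion.** The concern holds in a limited form. As written, the rule for justified deviations lets a difference in documentation enter the between-group comparison. The justified component, and any sum of *yes* and *justified*, can therefore differ between arms with identical prescribing. More frequent recording of reasons in the intervention arm is likely but not certain, so the likely direction favours the intervention.

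The size is not determined by the documents. The 1.2 to 16.8 points apply to the sum and rest wholly on assumed values for guideline adherence, for the share of deviations with a valid reason, and for documentation. The chances of significance further assume 1:1 allocation, 5 to 15 applicable criteria per patient and independence within patients.

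It would go too far to say that the whole Research Question 7 comparison is biased, or that a favourable result would be spurious. Strict adherence is not inflated by this route, and better recording of reasons may be a real benefit of the review. What the measure cannot do is separate that benefit from better prescribing. This concerns one of seven process questions and not the trial's primary outcome, but it is worth settling because the answer will be used to explain the trial result.

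**What to change.** Add a scoring and reporting instruction for Research Question 7, ideally before the records are assessed:

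1. Report the proportion of applicable criteria scored *yes* as its own between-group contrast, keeping *no information found* in the denominator in both arms so that fuller notes do not change the denominator through that answer.
2. Report *no, but this is justified*, *no* and *no information found* separately by arm. State that neither the justified share nor its sum with *yes* is to be interpreted as prescribing quality alone.
3. Add a sensitivity analysis, under the same rule in both arms, that does not credit reasons found only in study-pharmacist notes or recorded after the 6-month point. This requires the assessor to note the author type and date of each reason credited.

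The tool's answer options stay as they are. The cost is a little more scoring and analysis work. Two limits remain. *Yes* alone gives no credit for appropriate individualised deviations, which is why both components should be shown. The sensitivity analysis cannot remove reasons that a cardiologist recorded because a pharmacist raised the matter.
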